### Participants

#### Sample size

Based on the primary outcome measure (efficacy, safety and cost-effectiveness of nabiximols in outpatient treatment of cannabis dependence), a total sample size of 142 participants (71 per group) is required to achieve around 22% abstinence rates at 12-weeks for the placebo group (ascertained by average of previous drug administered clinical trials) and approximately 44% abstinence rates for the nabiximols group (based on clinical judgement of double the rate of abstinence than placebo) with 80% power (two-tailed) and α = 0.05.

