### Randomisation and blinding

An independent statistician created a randomisation schedule, which was then given to the lead trial pharmacist at each site. Participants are blindly randomised in a 1:1 ratio between groups, using the variable 8-block randomisation schedule of 80 codes per site to maintain blinding. Stratification occurs at each of the four sites (aiming for a 1:1 random allocation at each site). Randomisation and group allocation happen after enrolment (informed consent) and prior to Day 1 of the study, enabling study medications to be prepared by the study pharmacist at each site. The randomisation schedule and nabiximols and placebo canisters are only identifiable to trial pharmacists at each site, who themselves have no contact with participants. All participants, clinicians and researchers involved in service delivery, data collection and analysis remain blinded to group allocation (active or placebo) until the end of the study.

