	Rey Auditory Verbal Learning Task [62]	Retention of a 15 item word list presented on 5 occasions. Number of words recalled on each presentation, following presentation of a novel list of 15 words; and then after brief and long delays recorded. Recognition of target stimuli also assessed.	Research Interview: Weeks 0, 4, 24

#### Objective 1

To examine cannabis treatment efficacy outcomes, including changes in illicit cannabis use during treatment and treatment retention.Illicit cannabis use is quantified as self-reported number of days of illicit cannabis use and average daily amount of cannabis use in grams at the 4 weekly research interviews using modified Timeline Followback [40] techniques. The primary end-point is self-reported illicit cannabis use days during the maintenance phase of treatment (weeks 1-12). Objective measures of illicit cannabis use will be determined from weekly urine collection with quantitative analysis of urinary THC, THC-COOH, CBD and other cannabinoids. 4-weekly point prevalence abstinence during maintenance phase (weeks 1-4, 5-8, 9-12), and post-treatment period (week 24) will be ascertained by combining self-report data from researcher interviews and urinalysis.Treatment retention (days in protocol treatment) are recorded from clinical records. Participants who do not attend for more than two consecutive weeks are deemed to have dropped out of treatment, and the last scheduled day of dosing is calculated as the end of treatment date.

#### Objective 2

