## Statistical analyses

Chi square and ANOVA tests will be performed to identify any baseline covariates that differ between groups. Prior to carrying out primary and secondary analysis, the percentage of missing values in the raw dataset and Little’s MCAR test will be used to determine if multiple imputation of missing values is required (except for missing urine where cannabis use will be assumed to have taken place). The multiple imputation will be done if the percentage of missing values exceeds 5%.

All analyses will use Intention-to-treat, which is defined as any person who is randomised to one of the study arms and receives at least one dose of study medications. Mixed Models for Repeated Measures (MMRM) will compare groups on changes in outcome variables (cannabis use and secondary outcomes) in the medication phase with the multiply imputed dataset, (assuming that Little’s MCAR at Random test confirms the data to be missing at random). In addition, we will perform a sensitivity analysis based on only those with complete data, and compare results to that from the MI dataset analysis.

Adverse Events will be analysed using chi-square. A Cox proportional hazards model will compare retention in treatment between study arms, controlling for potential confounds. The impact of the intervention on post-medication outcomes will compare changes in cannabis use outcomes at baseline and at follow up between groups using MMRMs.

Family-wise error corrections will control for Type 1 errors where multiple comparisons are performed within a particular analysis where post hoc contrasts are performed to further explore interesting (significant) findings.

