## Study limitations

This study has a number of possible limitations. One issue relates to retention in study protocol. Participation in the study is voluntary, and study procedures span 24 weeks, including 13 weeks of study treatment interventions. The lengthy treatment duration in the study is generally longer than conventional treatment of cannabis dependence, and participants may be deterred from entering the trial or prematurely terminate study participation, which in turn may have implications in assessing effectiveness of treatment outcomes and research follow-up. Similarly, individuals enrolling in a medication study may have different levels of interest or commitment to the CBT in the study, which may enhance heterogeneity of outcomes.

The study uses a flexible dosing approach to medication. Whilst a fixed regimen – or indeed a structured comparison of different doses (e.g. high or low) is often used in many medication studies – experience from opioid agonist clinical and research practice highlights the need to tailor doses to individual requirements, reflecting differing physiological tolerance, adverse event profiles and behavioural characteristics of patients. Nevertheless, the different doses used may increase heterogeneity of outcomes and limit the ability to detect significant differences if there is indeed a major dose effect.

Measures of illicit cannabis use during treatment are the primary study outcome, with self-reported use (via the TLFB) as the primary endpoint. Participants may have a response bias and report inaccurate drug use to both clinicians and researchers. Whilst objective assessment of illicit cannabis use using urine drug screening should enhance self-report validity, it remains to be seen whether illicit cannabis use can be differentiated from prescribed nabiximols use. Various toxicological approaches are being examined to validate the identification of illicit cannabis use in nabiximols prescribed patients (to be described elsewhere).

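### The stated missing-data check, complete-case against multiple imputation, cannot show whether the use-days result is robust to informative dropout

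*Protocol article*

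**What the plan says.** The primary endpoint is self-reported days of illicit cannabis use over weeks 1 to 12, collected at the 4-weekly research interviews (Outcome and treatment process measures, Objective 1).

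The Statistical analyses section fixes how missing values are handled:

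- Multiple imputation (MI) is done if more than 5% of values are missing, followed by mixed models for repeated measures (MMRM) on the imputed data. MAR is to be supported by Little's test.
- One sensitivity analysis is named: "we will perform a sensitivity analysis based on only those with complete data, and compare results to that from the MI dataset analysis".
- A missing urine sample counts as cannabis use. No similar rule is stated for self-reported use days.
- The analysis population is everyone randomised who took at least one dose.

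The Study limitations section says that participants may "prematurely terminate study participation, which in turn may have implications in assessing effectiveness of treatment outcomes and research follow-up". The Study design section keeps all participants in the research interviews whether or not they finish treatment.

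**The concern.** A sensitivity analysis should vary the assumption that is in doubt. Here that assumption is MAR: given the recorded data, participants who miss an interview used cannabis no more than those who attended. The obvious threat is that people miss the interview because they are using more at that time, which is MNAR.

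Restricting to complete data does not relax MAR. If dropout depends on earlier recorded use, MI and MMRM can remain valid while the complete-case analysis does not. The restriction also removes members of the plan's own analysis population on a post-randomisation event, so the remaining arms need not be comparable.

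The plan treats retention as an efficacy outcome, so a difference in retention between arms is contemplated. The Background reports better treatment completion on nabiximols than on placebo in the earlier inpatient trial. If missingness differs by arm, the trial could report agreement as reassurance, or a gap as a warning, when neither says whether MAR holds.

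**Working it through.** **The plan's own figure.** The article says "a total sample size of 142 participants (71 per group) is required" for "around 22% abstinence rates at 12-weeks for the placebo group" and "approximately 44% abstinence rates for the nabiximols group", "with 80% power (two-tailed) and α = 0.05", with 1:1 allocation. With pooled variance and mean rate 0.33:

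n = [1.960 × √(2 × 0.33 × 0.67) + 0.842 × √(0.22 × 0.78 + 0.44 × 0.56)]² / 0.22² = (1.303 + 0.544)² / 0.0484 ≈ 70.5, so 71 per arm and 142 in total (power 80.3%).

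The figure reproduces. It concerns an abstinence proportion, contains no dropout allowance and implies no rate of missing data. Every missing fraction below is therefore an assumption.

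**Check 1: true difference zero.** Assumed inputs: three 28-day blocks, SD 8 days, within-person correlation 0.6, large sample. Dropout is tied to use in placebo and unrelated to use in nabiximols. At week 12, 45% (placebo) and 31% (nabiximols) are missing. Entries are nabiximols minus placebo, in days in the last block.

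| Dropout depends on | MAR-based | Complete-case | Gap |
|---|---|---|---|
| earlier recorded use (MAR) | -0.01 | +1.96 | 1.97 |
| current unrecorded use (MNAR) | +1.44 | +2.62 | 1.18 |

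The gap is larger where the primary is right than where it is wrong.

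**Check 2: true effect about -7.8 of 84 days.** Same SD and correlation, 35% missing, use-dependent dropout in placebo only.

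| Dropout depends on | MAR-based | Complete-case | Gap |
|---|---|---|---|
| earlier recorded use (MAR) | -7.7 | -2.8 | 4.9 |
| current unrecorded use (MNAR) | -6.1 | -3.0 | 3.1 |

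The complete-case result is nearly the same in both rows, although the primary is unbiased in the first and about 1.7 days off in the second (7.8 - 6.1).

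**Agreement.** Suppose everyone with missing data misses all three on-treatment interviews, and baseline predicts little. MI then fills the gaps from the participants who attended, which is in effect what complete-case does. The two agree and share any MNAR bias.

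**Range for the primary estimate**, placebo-only MNAR, true effect about -7.8:

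| Missing | MAR-based | Bias |
|---|---|---|
| 10% | -7.4 | 0.4 |
| 20% | -7.0 | 0.8 |
| 35% | -6.1 | 1.7 |

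With the same mechanism in both arms, bias in the difference is near zero. With the mechanism in nabiximols only, the bias would change sign and exaggerate the benefit.

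**What a delta adjustment shows.** If unrecorded use in nabiximols is d days per block worse than MAR predicts, the arm difference in that block moves by d × the fraction missing in that arm. At 30% missing, d = 2, 5 and 10 give 0.30 × 2 = 0.6, 0.30 × 5 = 1.5 and 0.30 × 10 = 3.0 days. The same d in both arms moves the difference by d × (nabiximols fraction - placebo fraction), which is zero at equal missingness. Both versions are therefore needed.

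**The case against.** The strongest reply is that this is an omission. The article condenses a longer plan and does not say that its sensitivity analysis is the sole one, and delta-adjusted or reference-based imputation is commonly left to a statistical analysis plan. A reader might infer that the trial has no MNAR analysis at all; the article alone cannot support that. What stands is narrower: the check the article does state is unsuited to the purpose it is given.

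Second, complete-case analysis does not always require missing completely at random. It can be valid when missingness depends only on covariates in the model. That is correct, and it limits the point to outcome-dependent dropout, which is the case of interest here.

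Third, the comparison is not empty. In several simulated MNAR settings the two estimates separate, and when the mechanism is equal in both arms they agree and both are close to the truth. This stands, but a gap is non-specific, because MAR dropout opens one too.

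Fourth, leaving treatment is not the same as missing a research interview, and interviews continue after treatment stops. This reduces the risk. It does not remove it, since the limitations section itself mentions research follow-up.

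Fifth, a reader might take the large complete-case errors (-2.8 or -3.0 against -7.8) as the likely error of the trial result. They are errors of the sensitivity analysis. The primary estimate moves far less, and only under arm-specific mechanisms that the article neither asserts nor rules out.

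Finally, counting a missing urine as use is a non-MAR rule. It applies to urine results, not to self-reported days, and is not a sensitivity analysis.

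**Conclusion.** The point holds in a limited form. The stated complete-case comparison cannot establish robustness to informative dropout: a gap may appear whether the primary analysis is valid or biased, and agreement does not exclude MNAR. The primary MI and MMRM analysis can stand; a claim of robustness resting on this check cannot.

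The size is unknown, because the article gives no dropout rate. Under the assumptions shown (SD 8, correlation 0.6, true effect about -7.8 of 84 days, placebo-only MNAR), bias in the primary estimate runs from about 0.4 days at 10% missing to 1.7 days at 35%, and is near zero when both arms share the mechanism. These figures illustrate and do not predict. The change is worth making because it is cheap, not because a large bias has been shown.

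**What to change.** In the analysis plan, if it does not already do so:

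1. Keep complete-case as a descriptive supplement and draw no robustness conclusion from it.
2. Make the sensitivity analysis of self-reported use days a delta-adjusted MI. Add increasing numbers of days to imputed values, capped at 28 per block, once in both arms and once in nabiximols only. Report the delta at which the conclusion changes.
3. Add a run that counts missing days as use days, matching the urine rule.
4. Optionally, add a reference-based run (missing nabiximols periods imputed from placebo) and use the weekly clinic timeline follow-back as auxiliary data.

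Items 1 to 3 cost plan wording and extra analysis runs. Item 4 needs new imputation models. Nothing changes in sample size, visits or data collection.

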## Study limitations

This study has a number of possible limitations. One issue relates to retention in study protocol. Participation in the study is voluntary, and study procedures span 24 weeks, including 13 weeks of study treatment interventions. The lengthy treatment duration in the study is generally longer than conventional treatment of cannabis dependence, and participants may be deterred from entering the trial or prematurely terminate study participation, which in turn may have implications in assessing effectiveness of treatment outcomes and research follow-up. Similarly, individuals enrolling in a medication study may have different levels of interest or commitment to the CBT in the study, which may enhance heterogeneity of outcomes.

The study uses a flexible dosing approach to medication. Whilst a fixed regimen – or indeed a structured comparison of different doses (e.g. high or low) is often used in many medication studies – experience from opioid agonist clinical and research practice highlights the need to tailor doses to individual requirements, reflecting differing physiological tolerance, adverse event profiles and behavioural characteristics of patients. Nevertheless, the different doses used may increase heterogeneity of outcomes and limit the ability to detect significant differences if there is indeed a major dose effect.

Measures of illicit cannabis use during treatment are the primary study outcome, with self-reported use (via the TLFB) as the primary endpoint. Participants may have a response bias and report inaccurate drug use to both clinicians and researchers. Whilst objective assessment of illicit cannabis use using urine drug screening should enhance self-report validity, it remains to be seen whether illicit cannabis use can be differentiated from prescribed nabiximols use. Various toxicological approaches are being examined to validate the identification of illicit cannabis use in nabiximols prescribed patients (to be described elsewhere).

## Conclusion

There is a need for more effective treatment approaches for cannabis dependent patients who are unable to discontinue their illicit use through psychosocial interventions alone. Longer-term agonist replacement treatment approaches rather than acute withdrawal management are likely to be more effective, with the combination of THC:CBD nabiximols preparation being potentially advantageous over synthetic THC analogues. This is the first large-scale outpatient RCT of nabiximols for this population, and has required the development of clinical and research methods specific to agonist treatment with a plant-derived cannabinoid formulation, building upon clinical research models previously used in opioid agonist treatment approaches.

## Abbreviations

ATOP: Australian Treatment Outcomes Profile
BPI: Brief Pain Inventory
BPRS: Brief Psychiatric Rating Scale
CBD: Cannabidiol
CBT: Cognitive behavioural therapy
CONSORT: Consolidated Standards of Reporting Trials
CRF: Clinical record form
CWS: Cannabis Withdrawal Scale
DASS-21: Depression, Anxiety and Stress Scale-21
DSMB: Data Safety Monitoring Board
HRQoL: Health related quality of life
ISI: Insomnia Sleep Inventory
NHMRC: National Health and Medical Research Council
ORBIT: Opioid Treatment Index- Crime
PGICS: Patient Global Impression of Change Scale
PHQ-15: Physical Health Questionnaire-15
QALY: Quality Adjusted Life Years
QID: Four times a day
RAVLT: Ray Auditory Verbal Learning Test
RCT: Randomised controlled trial
SF-36: Short form 36 health survey questionnaire
SMO: Study medical officer
THC: Tetrahydrocannabinol
TLFB: Timeline Follow Back
VAS: Visual Analogue Scale
